## Abstract

**Background:**

In chronic obstructive pulmonary disease (COPD) management, greater emphasis has been placed on symptomatic improvement and enhanced quality of life in patients. Manual therapy among respiratory rehabilitation programs has received much attention recently, with the publication of numerous studies. In South Korea, a method known as Chuna Manual Therapy (CMT) has been applied in the management of COPD patients and in clinical practice, but the clinical basis for safety and effectiveness is yet to be established. Therefore, rigorously designed randomized controlled trials are required. We aimed to evaluate the feasibility of assessing the add-on effect and safety of CMT administered with standard Western medicine therapy for the treatment of COPD.

**Methods:**

This is a randomized, single-blind, single-center clinical pilot trial. Patients with COPD receiving standard drug therapy are randomly divided into an experimental group (n = 20) and a control group (n = 20) at a 1:1 ratio. The experimental group receives CMT adding to the standard medical therapy once a week for 8 weeks. The control group receives only the standard drug treatment. The trial is conducted with an outcome assessor and statistician blinding. The primary outcome is the 6-minute walk test. The secondary outcomes include the pulmonary function test, the Modified Medical Research Council, visual analog scale for dyspnea, COPD assessment test, quality of life using the St. George's respiratory questionnaire, EuroQOL five dimensions questionnaire, and Korean pattern identification questionnaire. Adverse events are also be evaluated.

**Conclusions:**

The results of this study will provide the feasibility of a large-scale clinical trial to establish high-quality clinical evidence of CMT for COPD.

**Trial registration:**

Korean Clinical Trial Registry (http://cris.nih.go.kr; registration number: KCT0006119).

## Introduction

1

Chronic obstructive pulmonary disease (COPD) is a common respiratory disease characterized by persistent respiratory symptoms and airflow limitation.^[1]^ Immediate effect of manual therapy (MT) on respiratory functions and inspiratory muscle strength in patients with COPD. Chronic inflammation and obstruction of airflow in COPD reduce the interstitial elasticity, while the prolonged contraction of respiratory muscles leads to an increased ventilatory flow demand, placing a substantial burden on the respiratory muscles.^[2,3]^ The consequent pulmonary hyperinflammation or increased respiratory demand causes breathing distress, a change in breathing patterns, or a fall in motor ability. As a result, COPD patients experience limited and reduced physical activity, which may cause skeletal muscle wasting, sarcopenia, or cachexia.^[4]^ In recent studies, therefore, emphasis has been placed on nonpharmacological therapy, including respiration rehabilitation, for managing the underlying symptoms of COPD.^[1]^ In respiration rehabilitation, the main focus has been on exercise therapy, and recently, MT has received much attention. MT has been shown to indirectly improve motor ability and lung function in patients by increasing thoracic wall flexibility and chest exercise.^[5,6]^

In South Korea, Chuna manual therapy (CMT) has been used for the treatment of various diseases, including musculoskeletal conditions. CMT is performed by a Korean medicine doctor who uses his or her hands or other parts of the body and an assistive tool such as the Chuna table to provide effective stimuli to the patient's body for the treatment of structural or functional problems. While it may share similarities with other manual therapies performed in different countries, the Korean CMT has advanced as a unique technique that integrates the outstanding manual therapies of China, Japan, India, and the US based on the traditional Chuna technique with the Korean traditional meridian theory.^[7]^ CMT is generally applied in various treatments of the musculoskeletal system,^[8,9]^ but its effects have also been reported for headache, tinnitus, and digestive diseases.^[10–13]^ MT in COPD patients has been investigated with systematic reviews^[14–18]^; however, the clinical efficacy of CMT has not yet been studied. Thus, this study aimed to investigate the safety and effectiveness of CMT in COPD through a small-scale, exploratory clinical study for the combined treatment of CMT and standard drug therapy.

## Methods

2

### Objective and design

2.1

The primary purpose of this study is to verify the effectiveness and safety of CMT in combination with Western medicine therapy for COPD. The patients receiving COPD treatments are randomized into two groups: the experimental group for a combination of CMT and Western medicine therapy and the control group for Western medicine therapy only, while the intervention is performed for 8 weeks, once a week. The study will be conducted as a prospective, single-center, single-blinded, exploratory clinical study, and based on the results, the sample size for future large-scale clinical trials will be determined. The feasibility of the study protocol will also be evaluated. A flow diagram of this study is shown in Figure 1.

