#### Exclusion criteria

2.3.2

1.Individuals with comorbidity of severe respiratory disease other than COPD (cystic fibrosis, pneumonia, interstitial lung disease, lung cancer, etc)2.Individuals with a history of alcohol or other substance abuse or dependency3.Individuals showing a clinically significant disease or disorder of the liver, kidneys, cardiovascular system, respiratory system, endocrine system, and central nervous system, based on the results of the physicochemical test and clinical examination, and those with a history of malignant tumor or mental disorder (here, individuals without 5-year postoperative recurrence are allowed to participate)4.Individuals showing a change of drug use within the past three months prior to the present study5.Individuals who are unable to walk independently6.Individuals who have received kinetic, physical, or MT related to respiratory rehabilitation within the past month7.Individuals who are currently receiving an oxygen therapy8.Individuals with symptoms that prevent the use of CMT9.Individuals who are pregnant or planning a pregnancy10.Individuals who are deemed unsuitable for the clinical study by the principal investigator

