### Sample size

2.7

This study is a small-scale, prospective, preliminary clinical study to verify the feasibility and treatment effects of a large-scale clinical trial. Therefore, an accurate sample size must not be determined. Based on a previous study suggesting a minimum of 12 subjects per group for a pilot study in biomedical science,^[28]^ the number of subjects to be recruited and the minimum range for efficacy evaluation is set as 16, considering a 20% dropout rate, a total of 40 subjects will be recruited.

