## Discussion

3

The present protocol is the first attempt in South Korea to verify the effectiveness and safety of CMT for COPD. The effects of respiration rehabilitation are widely known, and exercise therapy is actively applied in clinical practice for the management of functional abilities in COPD patients.^[1]^ Exercise therapy is the optimal management therapy among non-pharmacological therapies, and it plays a role in improving the quality of life of COPD patients by improving symptoms such as dyspnea.^[29]^ However, voluntary participation in exercise therapy is not easy for patients with severe breathing difficulties. Therefore, the interest in MT performed by experts is increasing, and studies on COPD with MT have been conducted.^[14–18]^ MT plays a role in expanding the rib cage and reducing respiratory muscle shortening.^[30]^ Studies have shown a major effect on the improvement of motor performance in patients with COPD.^[16]^ The CMT used in this study is a technique involving 10 to 15 minutes of exercise conducted by a trained professional Korean medicine doctor, and as the patient can receive the therapy while lying on the bed, the technique is advantageous in that it can be performed regardless of the severity of the patient.

The results of randomized controlled trial (RCT) based on this protocol are anticipated to contribute to promoting the research on CMT in COPD treatment as well as being the starting point in establishing the clinical basis. Furthermore, the addition of an effective treatment for COPD, a chronic, intractable disease, will prove useful for clinicians and in the management of COPD patients.

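### The stated primary purpose includes verifying the safety of CMT, which an exploratory pilot with 20 CMT patients cannot do

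*Protocol article*

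**What the plan says.** Section 2.1 (Objective and design) sets the aim: "The primary purpose of this study is to verify the effectiveness and safety of CMT in combination with Western medicine therapy for COPD". The opening of the Discussion describes the protocol in the same terms, again using the verb *verify* for both effectiveness and safety.

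Other parts of the article are more modest. The Background of the Abstract says that the aim is to judge whether the add-on effect and safety can feasibly be assessed. The Abstract's Conclusions speak only of the feasibility of a large trial. The Introduction says that safety and effectiveness will be investigated in a small exploratory study. Section 2.1 itself calls the study exploratory, intends it to size a later trial, and adds feasibility as something to be evaluated as well.

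On numbers, patients are "randomly divided into an experimental group (n = 20) and a control group (n = 20) at a 1:1 ratio" (Abstract, Methods). Section 2.7 bases this on "a previous study suggesting a minimum of 12 subjects per group for a pilot study in biomedical science", then says that "the minimum range for efficacy evaluation is set as 16" and that, "considering a 20% dropout rate, a total of 40 subjects will be recruited". No event rate and no precision target for safety is given. Section 2.6 has adverse events checked at every visit and graded by CTCAE.

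**The concern.** To verify safety is to reach a conclusion: that harm above some tolerable level has been ruled out. Twenty exposed patients cannot support that conclusion for any event short of a very common one, even if the trial runs without incident. The article therefore states two aims that differ in kind, feasibility and verification, and gives the name of primary purpose to the one that the design cannot deliver.

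The primary purpose is what the final report will be written against. A pilot in which no harmful event occurs could be reported as having met its purpose on safety, when the data remain compatible with a substantial event rate. Section 3.1 expects a full-scale multicentre trial after this analysis, so an overstated safety conclusion could carry into its planning. This point concerns safety only. It does not address power for the 6-minute walk test.

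**Working it through.** **Inputs from the article**
- Patients allocated to CMT: 20 (Abstract, Methods; section 2.7).
- Number per group for efficacy evaluation: 16; dropout: 20%; total: 40 (section 2.7).
- Adverse event rates: none given. The rates in step 3 are assumptions chosen to show a range.

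**Step 1. Reproduce the plan's own figure.** 16 / (1 − 0.20) = 20 per group, and 2 × 20 = 40. The stated total is reproduced, so the arithmetic of the sample size is not at fault.

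**Step 2. What an event-free CMT arm would show.** With zero events in n patients, the upper limit p solves (1 − p)^n = α. No assumption about the true rate is needed.
- One-sided 95%: 1 − 0.05^(1/20) = 0.139, or 13.9%.
- Two-sided 95% exact (Clopper–Pearson): 1 − 0.025^(1/20) = 0.168, or 16.8%.

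**Step 3. Chance that an event is not seen at all.** For true rate p this is (1 − p)^20.

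| Assumed true rate | No event in 20 | At least one event in 20 |
|---|---|---|
| 0.5% | 90.5% | 9.5% |
| 1% | 81.8% | 18.2% |
| 2% | 66.8% | 33.2% |
| 5% | 35.8% | 64.2% |
| 10% | 12.2% | 87.8% |

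**Step 4. Exposure needed to exclude a given rate.** With zero events and a one-sided 95% limit, n is ln(0.05) / ln(1 − p), rounded up:
- 59 exposed patients to exclude 5%
- 149 to exclude 2%
- 299 to exclude 1%

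The CMT arm is about one third of the size needed for the least demanding of these (20 / 59 = 0.34).

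**The case against.** The strongest reply is that one verb has been lifted out of text that already limits it. The article calls the study exploratory, preliminary and small, and the Abstract concludes only on feasibility. No passage says that an event-free pilot would be reported as proof of safety. The zero-event limit would apply to any arm of 20. Exact intervals are also a detail that a condensed article may leave to the full protocol or analysis plan.

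Much of this stands. It makes the matter one of wording, and the absence of an interval is not itself a fault. What remains is that the article affirmatively names verification as the primary purpose and repeats it in the Discussion. The modest statements elsewhere do not cancel that; they leave two aims that cannot both govern the report.

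Three stronger readings are tempting, and the documents do not support them.

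- **Severity.** The Discussion says that "the technique is advantageous in that it can be performed regardless of the severity of the patient", while section 2.3.2 excludes "Individuals who are currently receiving an oxygen therapy" and "Individuals who are unable to walk independently". A reader might infer that the article extends a safety finding to patients who were never exposed. In context, the sentence contrasts CMT with exercise therapy and rests on the patient lying down. It concerns whether the technique can practicably be delivered, and it is not a planned conclusion. Section 2.3.1 sets no FEV1 limit, so patients with severe airflow limitation who walk independently and are not on oxygen may enter. This is a minor note only: the trial will not test the sentence in the excluded groups.
- **A denominator of 16.** A reader might compute the limits on 16 patients. That is the number for efficacy evaluation. A patient who leaves after a CMT session has still been exposed, and nothing in the article says that dropouts leave before treatment.
- **A between-arm test.** A reader might judge safety by what a significance test on adverse events could detect. The article specifies no such test.

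**Conclusion.** The statement of purpose is wrong as written with respect to safety. With 20 patients exposed and no events, a true rate of up to 13.9% (one-sided 95%) or 16.8% (two-sided exact 95%) is not excluded. An event with an assumed true rate of 5% would go unseen in 36% of such trials. The limits depend only on the number exposed. They take all 20 allocated patients as receiving at least one session, which is the favourable case, since fewer exposed patients would raise them. The 36% depends on the assumed 5%, because the article gives no rates.

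The pilot's size, conduct and eligibility are not called into question. The defect is an overstatement in the objective that should be corrected because it governs what the trial may conclude.

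**What to change.** 1. In section 2.1 and the Discussion, replace the verb *verify*, as applied to safety, with a preliminary description of adverse events, consistent with the feasibility aim in the Abstract.
2. Report the number of patients with events in each arm with an exact 95% interval. Use patients who received at least one CMT session as the CMT-arm denominator. This can be placed in the article, the full protocol or the analysis plan.
3. State in advance that an event-free CMT arm of 20 does not exclude a true rate of about 14 to 17%.
4. As a minor edit, note beside the severity sentence in the Discussion that it concerns delivery and is not tested here in oxygen users or in patients who cannot walk independently.

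The cost is a few changes of wording and one interval per reported event type. Sample size, eligibility and data collection are unaffected. The downside for the sponsor is a less favourable safety claim.

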**Figure 1 F1:**
[figure not shown]
Flowchart of the study. CMT = Chuna manual therapy; WM = Western medicine.

### Randomization, allocation, and blinding

2.2

The patients are randomized into two groups: the experimental group (standard Western medicine therapy + CMT) and the control group (standard Western medicine therapy), in a 1:1 ratio. For randomization, an independent statistician produced a random number table using Microsoft Windows SAS ver. 9.1.3 (SAS Institute Inc, NC, Cary) and allocates random numbers to the patients.

The random number table produced using the SAS and the allocation table for the test or the control group based on the random numbers are stored by the statistician until discontinuation or termination of the study, while the principal investigator does not request for the data.

The subjects in this study are given the screening number as they submit the signed written consent for participation in the clinical study after receiving an explanation regarding the study.

The subjects finally selected through the screening test are given the registration number, and based on the random number table stored by the statistician, each subject is allocated to the group in line with the subject registration number. This study aims to investigate CMT as an add-on to standard drug therapy, and it will be conducted as a single-blinded study with a control group receiving only standard drug therapy. Neither the subjects nor the Korean medicine doctor practitioners is blinded. The principal investigator and assessor who collecting the data are blinded to each group allocation.

### Patients

2.3

#### Inclusion criteria

2.3.1

1.Patients aged between 40 and 80 years2.Patients who satisfy the COPD clinical diagnostic criteria (forced expiratory volume in one second [FEV1] / forced vital capacity [FVC] < 0.70 on the Spirometry)^[1]^ and receiving the standard drug therapy3.Patients who voluntarily signs and submits the written consent for participation in the present clinical study

#### Exclusion criteria

2.3.2

1.Individuals with comorbidity of severe respiratory disease other than COPD (cystic fibrosis, pneumonia, interstitial lung disease, lung cancer, etc)2.Individuals with a history of alcohol or other substance abuse or dependency3.Individuals showing a clinically significant disease or disorder of the liver, kidneys, cardiovascular system, respiratory system, endocrine system, and central nervous system, based on the results of the physicochemical test and clinical examination, and those with a history of malignant tumor or mental disorder (here, individuals without 5-year postoperative recurrence are allowed to participate)4.Individuals showing a change of drug use within the past three months prior to the present study5.Individuals who are unable to walk independently6.Individuals who have received kinetic, physical, or MT related to respiratory rehabilitation within the past month7.Individuals who are currently receiving an oxygen therapy8.Individuals with symptoms that prevent the use of CMT9.Individuals who are pregnant or planning a pregnancy10.Individuals who are deemed unsuitable for the clinical study by the principal investigator

### Intervention

2.4

The CMT is performed on the primary and accessory respiratory muscles. The CMT in this study is given to all subjects in the same way from the first to the tenth method, the details of which are as follows.

1.Cervical relaxation: The patient is in a supine position, and the therapist uses both hands to cover the patient's neck and turns the C1-7 spinous process and splenius muscle with pressure using the second and third fingers.2.Occipitocervical junction relaxation: The patient's head is made to protrude from the bed, and the therapist uses the second, third and fourth fingers to push the occipitocervical junction with pressure.3.Trapezius muscle relaxation: The therapist uses the thumb and the second finger to lift the trapezius muscle on both sides, and pushes the muscle with the thumb with pressure for relaxation.4.Clavicle relaxation: The therapist uses the thumb to repeatedly rub the upper and lower sides of the clavicle for relaxation.5.Pectoral major and latissimus dorsi muscle relaxation: The therapist stretches the hands and with pressure on the thumb pushes the entirety of the pectoral major muscle with pressure for relaxation. Next, using the thumb, the therapist pushes with pressure the insertion point of the latissimus dorsi muscle vertically below the armpit.6.Rectus abdominal muscle relaxation (via upper limbs): The therapist holds both hands of the patient to help him or her stretch the arms upwards, then stretch the feet while breathing out (1 set). Next, the patient is guided to bring the feet back towards the body while breathing out (2 sets) → The two sets are repeated.7.Quadratus lumborum and intercostal muscle relaxation (via upper limbs): In position 6, the therapist pulls the patient's arm to the left. Here, the patient is instructed to move their feet to the left (one set). Next, the therapist pulls the patient's arm to the right, while the patient moves the feet to the right (two sets) → The two sets are repeated.8.Thoracic breathing relaxation (via pressure on the humeral head): The therapist places the palms on the patient's humeral head on both sides, and applies pressure as the patient breathes in and relaxes as the patient breathes out. This process is repeated.9.Breathing relaxation (via pressure on pectoral major muscle): The therapist places the palms on the patient's pectoral major on both sides, and applies pressure as the patient breathes in and relaxes as the patient breathes out. This process is repeated.10.Abdominal trapezius and thoracolumbar paraspinal muscle relaxation: The therapist places the palms on the patient's abdominal trapezius muscle and thoracolumbar paraspinal muscle, and applied pressure in a soft sliding motion from the area around C7, along with the rectus abdominis muscle, then relaxes toward the waist area for overall muscle relaxation.

The CMT is performed by a Korean medicine doctor with over 3 years of experience over 15 minutes.

### Outcome measures

2.5

#### Primary outcome

2.5.1

Primary outcome is the 6-minute walk test (6-MWT). The 6-MWT is a relatively simple and economic test that measures the distance the patient can walk on a flat, hard surface for 6 minutes. The test is commonly used to assess motor function in COPD patients,^[19]^ and it has been regarded as a crucial indicator of exercise tolerance in COPD patients across numerous studies.^[20–23]^

The clinical trial process in presented in Table 1.

**Table 1 T1:**
[figure not shown]
Trial schedule.

#### Secondary outcomes

2.5.2

Secondary outcomes include the pulmonary function test, the Modified Medical Research Council,^[24]^ and the visual analog scale for measuring respiratory distress. The St. George's Respiratory Questionnaire,^[25]^ a COPD assessment test,^[26]^ and EuroQOL five dimensions questionnaire (EQ-5D),^[27]^ are used to measure the quality of life. To classify the idiopathic types of COPD and evaluate treatment efficacy, pattern identification is carried out.

### Safety

2.6

Adverse events (AEs) refer to undesirable, unintended signs, symptoms, or diseases that occur during clinical trials and do not necessarily have causal relationships with the treatments used in the trial. The presence of AEs should be checked at every visit. The severity of AEs is measured using the Common Terminology Criteria for Adverse Events (CTCAE); Grade 1 (Mild): The normal daily activities (functions) are not prevented with only minimal discomfort and the subject can tolerate the symptoms; Grade 2 (Moderate): the normal daily activities (functions) of the subject are significantly inhibited; Grade 3 (Severe or medically significant): The normal daily activities (functions) of the subject are completely inhibited; Grade 4 (life-threatening consequences); Grade 5 (death related to AE). A serious adverse event (SAE) refers to one of the following AEs occurring in a clinical study participant during a clinical trial:

1.death or danger to life;2.hospitalization or extension of hospital stay due to an AE;3.permanent or significant failure or degradation of function;4.development of fetal malformations or abnormalities; and5.other medically important situations.

In the case of SAEs, investigators should report to the sponsor very quickly (usually within 24 hours).

